##### Perceived chewing ability

Twenty food items are to be assessed for the participants’ perceived ability to bite and chew food using a four-point rating scale [29]. The ratio of number of food items that a participant answers “can chew well,” which represents the highest rating for the 20 food items, is calculated to give a score for self-perceived chewing ability.

##### Masticatory performance

Mixing ability is evaluated using a color-changeable chewing gum (Xylitol Masticatory Performance Evaluating Gum; Lotte Co., Ltd., Tokyo, Japan) [30]. The participants are instructed to chew the gum depending on their preference, using 100 chewing cycles, at a rate of once per second. Mixing ability is measured by a colorimeter. Shearing ability is evaluated using a test gummy jelly (Test Gummy Jelly for Evaluating Masticatory Performance; UHA Mikakuto Co., Ltd., Osaka, Japan) [31]. The participants are instructed to chew the test gummy jelly using 30 chewing cycles, depending on their preference. Shearing ability is measured by a visual scoring method [32].

##### Patient self-assessment of dentures

Patients make a self-assessment of their dentures using the Patient’s Denture Assessment (PDA) [33]. The PDA comprises 22 items covering six subscales classified as function, lower denture, upper denture, expectation, aesthetics and speech, and importance. Each item in the questionnaire is rated using a 100-mm visual analog scale.

##### Assessment of mild cognitive impairment

Mild cognitive impairment is to be assessed with the Japanese version of the Montreal Cognitive Assessment (MoCA-J) [34]. The MoCA-J comprises 16 items covering eight domains: visuospatial/executive, naming, memory, attention, language, abstraction, delayed recall, and orientation. Low educational attainment is corrected for by adding 1 point to the participant’s final score for ≤12 years of formal education. The highest possible score is 30, with a score of 26 or above indicating normal cognitive function.

##### Functional capacity

Maintenance of competence is evaluated with the Japan Science and Technology Agency Index of Competence (JST-Index of Competence), developed from the Tokyo Metropolitan Institute of Gerodontology Index of Competence [35–37]. The JST-Index of Competence comprises 16 items and four categories classified as utilization of new equipment, information collection, management of daily life, and social engagement. Higher scores indicate better functional status.

### Criteria for withdrawal

Patients will be withdrawn from the study in the event of any relevant deterioration in health likely to affect participation, if they withdraw their consent, or if they die.

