### Sample size estimation

The sample size was determined based on the two primary outcomes: changes in the weight of fruit and vegetable intakes and in the weight of protein intake. In case of change in the weight of fruit and vegetable intakes, 29 individuals per group would provide 80 % power to detect a difference of 125 g per day in intake, with a two-sided test at a 0.05 level of significance for the primary outcome. In case of change in the weight of protein intake, 30 individuals per group would provide 80 % power to detect a difference of 15 g per day in protein intake, with a two-sided test at a 0.05 level of significance for the primary outcome. We also anticipated a 15 % rate of loss to follow-up. Accordingly, we adjusted our target baseline sample size to 35 per group.

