### Randomization and allocation

Eligible study participants are to be randomly assigned to the dietary intervention group or the control group in an alternate fashion. The randomization sequence has been established with block sizes of 10 and an allocation ratio of 1:1 before recruitment commences and is to be concealed in opaque consecutively numbered envelopes. After the decision on participants’ enrollment, the envelopes will be opened. Patient enrollment and randomization will be undertaken by two outcome assessors (HS and NA). Participants and clinicians will be blinded to the group allocation of each participant. The participants will be given repeated instructions not to reveal their group allocation to clinicians. Any questions from participants during the intervention period will be answered by the outcome assessors (AJ, HS, and NA).

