### Statistical analysis

All analyses are to be based on the initial treatment assignment (intention to treat). Missing data will be replaced with multiple imputation to primary and secondary outcome variables. Differences between the groups at 3 and 6 months and within-group changes are to be compared using the paired *t* test. All statistical analyses will be performed using IBM Statistical Package for the Social Sciences (SPSS) Statistics version 17.0 software. A significance level of 0.05 is used for each test.

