## Discussion

This randomized controlled trial is designed to demonstrate the effect of simultaneous simple dietary advice and provision of new complete dentures in combination on dietary intake in edentulous individuals who request new dentures. It is hypothesized that a combination of provision of new complete dentures and simple dietary advice would improve nutrient intake among edentulous individuals.

Whereas in previous clinical research, nutritional intervention consisted of one-to-one counseling sessions with a nutritionist [1], the nutritional intervention in the present study consists of dentists giving participants a pamphlet along with a standardized detailed explanation of its contents. In a cohort study designed to determine if a combination of denture fixative use and dietary simple advice in the form of printed government-issued pamphlets would improve participants’ diets, fruit and vegetable intake was reported to improve over a 30-day period [3]. The researchers expected that this intervention would have a long-term effect on the basis that once a dietary choice is made, it is likely to continue.

Both participants and clinicians are blinded in this study so that neither will be aware of the allocated intervention. Nevertheless, the two outcome assessors (HS and NA) of the three outcome assessors (AJ, HS, and NA) will implement the randomization and allocation. These two outcome assessors also deliver advice, although they will not give complete denture treatments. Because these two outcome assessors are also delivering advice, neither outcome assessors nor those who deliver advice are blinded, which may cause bias. However, the bias against delivering advice has a smaller influence on the results of the research than the bias against giving treatments. Moreover, the outcomes assessed in this research consist of patient-reported outcomes and objective outcomes. Thus, only a small number of outcome assessors’ subjective outcomes are included, which leads to less possibility of observation bias.

An exclusion criterion for fruit and vegetable intakes at baseline is not set. Thus, participants whose fruit and vegetable intakes at baseline are already high might be included. However, it is reported that the mean consumption of vegetables in Japanese edentulous patients is lower than the Japanese government recommended vegetable intake of 350 g/d [38].

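### Health deterioration leads to withdrawal from the study, not only from study procedures, so obtainable outcomes may be lost for a reason related to diet

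*Protocol article*

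**What the plan says.** The Criteria for withdrawal section gives three reasons for leaving the trial. The first is a rule about health: "Patients will be withdrawn from the study in the event of any relevant deterioration in health likely to affect participation". The other two follow in the same sentence: "if they withdraw their consent, or if they die". The section does not distinguish stopping study procedures from stopping follow-up. It sets no threshold for a relevant deterioration and does not say who judges it.

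The Statistical analysis section states "All analyses are to be based on the initial treatment assignment (intention to treat" and adds "Missing data will be replaced with multiple imputation to primary and secondary outcome variables".

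On timing, the Interventions section places the two advice sessions at the try-in and delivery appointments, with denture adjustments continuing afterwards as needed. The Outcome measures section sets assessments at baseline, 3 months and 6 months.

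On blinding, the Randomization and allocation section says "Participants and clinicians will be blinded to the group allocation of each participant", while the Discussion concedes that "neither outcome assessors nor those who deliver advice are blinded, which may cause bias".

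The Sample size estimation section plans 35 per group, allowing for a 15% "rate of loss to follow-up".

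**The concern.** Withdrawn consent and death end data collection unavoidably. Deterioration in health does not. Some participants who become unwell could still complete a questionnaire, and the primary outcomes come from one that is self-administered (the BDHQ). Removing them from the study gives up data that intention to treat would want.

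The reason for the loss is not neutral either. The Background section argues that poorer intake is likely to lead to ill health and that inadequate nutrient intake goes with weight loss and frailty. Deteriorating health is therefore plausibly related to fruit, vegetable and protein intake. It is related more directly to secondary outcomes such as nutritional status, body weight, cognition and functional capacity. A rule that removes people because their health declined can remove the poor values these measures are meant to record. If such removals differ between arms, the comparison is biased to the extent that imputation does not recover the missing values.

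**Working it through.** **1. Setting the sections side by side.** The withdrawal rule ends participation in the study. The analysis section keeps everyone in the arm assigned and imputes what is missing. The two can operate together, but the first creates missing values that the second must then model. A participant withdrawn before month 3 has only baseline data from which to impute, and the deterioration itself is not among the scheduled measurements. A participant withdrawn between months 3 and 6 also contributes month-3 data, so the imputation is better informed.

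**2. The plan's own allowance for loss.** Inputs from Sample size estimation: 30 per group needed for protein, 15% loss, target 35 per group.
- 30 × 1.15 = 34.5, rounded up to 35, which is the stated figure.
- 30 / 0.85 = 35.3, rounded up to 36, which is the usual formula.
- 35 × 0.85 = 29.75 expected completers, giving about 79.7% power for protein (two-sided 0.05, with the standard deviation implied by 30 per group at 80% power).

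The shortfall is trivial. It comes from how the allowance was calculated, not from the withdrawal rule.

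**3. Illustration for fruit and vegetables.** Suppose k participants in one arm only are withdrawn for health, and each has a true intake D g/day below the imputed value. With 35 in the arm, the arm mean is too high by

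bias = k × D / 35.

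The documents give neither k nor D. Take D = 125 g/day (an assumption, set equal to the target difference) and k from 2 to 5. The upper end assumes that the whole planned loss, 0.15 × 35 = 5.25 or about 5, is due to health.
- k = 2: 2 × 125 / 35 = 7.1 g/day, or 6% of 125.
- k = 5: 5 × 125 / 35 = 17.9 g/day, or 14% of 125.

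If both arms lost k participants with the same D, the biases would cancel in the difference.

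**4. Illustration for protein.** Suppose a fraction f of one arm is lost and those lost differ from the rest of that arm by D g/day. The complete-case difference shifts by f × D. With f from 0.05 to 0.15 and D from 5 to 15 g/day (all assumed), the shift runs from 0.05 × 5 = 0.25 to 0.15 × 15 = 2.25 g/day, or 2% to 15% of the 15 g/day target. Imputation would remove part of this.

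**5. Scale against sampling error.** No standard deviation is stated. The value implied by 29 per group, 125 g/day and 80% power is 125 × √(29/2) / (1.960 + 0.842) ≈ 170 g/day. The standard error of the arm difference at 35 per arm is then 170 × √(2/35) ≈ 41 g/day. The illustrated biases are 7.1/41 ≈ 0.17 and 17.9/41 ≈ 0.44 standard errors.

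**The case against.** The case for leaving the rule alone has several parts.

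- **The rule is qualified.** It covers only deterioration likely to affect participation. Blood sampling, chewing tests and bioimpedance need attendance, and someone whose cognition has declined may not give a reliable questionnaire. This stands: the number of recoverable outcomes is unknown, and the remedy must be limited to those who are able.
- **Loss is planned for and imputed.** Imputation can condition on baseline and month-3 intake, nutritional status, weight, cognition and function. This stands in part. A reader might infer that the rule contradicts intention to treat, but analysis by assignment with imputation is stated. What remains is dependence on health or diet that was not measured.
- **An article condenses.** Follow-up after withdrawal may be described in a fuller document. That could settle the matter, but the article does state a rule, and on its face the rule ends participation in the study.
- **The illustrated bias is small and assumed.** This stands: even the extreme case is under half a standard error.

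A reader might also infer three stronger points that the document does not support. The first is that unblinded staff decide on withdrawal. No decision-maker is named; assessors and advice-givers are unblinded, but treating dentists are said to be blinded, so an unblinded decision is possible and not stated. The second is that only data collection remains after denture delivery; adjustments continue, and a withdrawal can also fall before the second advice session. The third is that the rule leaves the trial short of completers; 29.75 against 30 is negligible and has another cause.

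**Conclusion.** The point holds in a limited form. The protocol article withdraws participants from the study for deteriorating health, which as written ends outcome collection for a reason its own Background links to intake and nutritional status. This weakens the intention-to-treat aim, and imputation restores it only as far as the observed data explain who was lost. The missing threshold and unnamed decision-maker leave room for judgement that could be influenced by knowledge of the arm, though the document does not say that this will happen.

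The size of any bias cannot be determined from the document. The 7 to 18 g/day for fruit and vegetables and the 0.25 to 2.25 g/day for protein rest wholly on assumed one-arm loss and assumed deficits, and show scale only. The case for change is that some of the loss is avoidable at little cost, not that a large bias has been shown.

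**What to change.** Reconcile the Criteria for withdrawal section with the Statistical analysis section in one paragraph:

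- Separate stopping study procedures from stopping data collection.
- End data collection only on withdrawn consent or death.
- After health deterioration, record the date and reason. Where the participant is able and still consents, continue to seek the 3- and 6-month BDHQ and other feasible questionnaires, remotely if needed.
- Have the decision made or confirmed by someone blinded to allocation, such as the treating dentist.

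The cost is a small amount of staff time. A few questionnaires would be completed in a different mode and would miss the on-site completeness check described under Outcome measures, so the mode should be recorded. No change to clinical care is implied, and no view is taken on when study procedures should stop.

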### Sample size estimation

The sample size was determined based on the two primary outcomes: changes in the weight of fruit and vegetable intakes and in the weight of protein intake. In case of change in the weight of fruit and vegetable intakes, 29 individuals per group would provide 80 % power to detect a difference of 125 g per day in intake, with a two-sided test at a 0.05 level of significance for the primary outcome. In case of change in the weight of protein intake, 30 individuals per group would provide 80 % power to detect a difference of 15 g per day in protein intake, with a two-sided test at a 0.05 level of significance for the primary outcome. We also anticipated a 15 % rate of loss to follow-up. Accordingly, we adjusted our target baseline sample size to 35 per group.

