### Interventions

All patients receive complete denture treatments. The technique used to create a complete denture involves primary and secondary impressions, recording of jaw relationships using occlusal rims, one or two trial insertions, and delivery of the new complete dentures. After delivery, adjustments to the dentures are made until both participant and clinician deem that no further adjustment is necessary. The new complete dentures are made by three dentists with 10–14 years of clinical experience (YK, MK, and MI). They will give complete denture treatments, but will neither deliver dietary advice or advice on care and maintenance of dentures nor assess outcomes. Participants will be randomly assigned to the three dentists.

Participants in the dietary intervention group receive 20 minutes of coordinated dietary advice in the form of an explanation of a pamphlet prepared with reference to the geriatric version of the Japanese Food Guide Spinning Top published by the Japanese Ministry of Agriculture, Forestry and Fisheries. The pamphlet is then given to the participant. If a participant does not prepare his or her own meals, the person who does the cooking receives the dietary advice as well.

Participants in the control group receive 20 minutes of coordinated advice for care and maintenance of dentures in the form of an explanation of a pamphlet prepared with reference to the guidelines published by the American Collage of Prosthodontics [23], after which the pamphlet is provided to the participant. The advice on diet and care and maintenance of dentures is provided by the two outcome assessors (HS and NA). The two-time deliveries of advice in the dietary intervention and control groups are designed to fit with dental appointments for try-insertion and delivery of new dentures.

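### The between-group t test at 3 and 6 months leaves out baseline intake, although it is collected and the trial is sized on changes in intake

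*Protocol article*

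**What the plan says.** - **Sample size estimation** bases the trial on "changes in the weight of fruit and vegetable intakes and in the weight of protein intake". For fruit and vegetables, "29 individuals per group would provide 80 % power" "to detect a difference of 125 g per day in intake". For protein, "30 individuals per group would provide 80 % power" for a 15 g/day difference. Both use alpha 0.05, two-sided. Allowing for 15% loss, the target is 35 per group. No SD is stated.
- **Statistical analysis** fixes the comparison: "Differences between the groups at 3 and 6 months and within-group changes are to be compared", by t test. It names no covariate, no between-group comparison of change and no model.
- **Outcome measures** schedules every outcome except antioxidant capacity at baseline, 3 months and 6 months, so each participant should have a baseline value for the primary intakes.
- **Discussion** notes that no baseline intake limit applies: "Thus, participants whose fruit and vegetable intakes at baseline are already high might be included".
- **Interventions** adds that "Participants will be randomly assigned to the three dentists". These dentists neither give advice nor assess outcomes.

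**The concern.** Two things do not fit together. The trial is sized on a difference in change, but the sentence that fixes the analysis mentions change only within groups and puts the between-group comparison at the visits. Within-group changes cannot test the null hypothesis in the Background, which concerns a difference between groups. On the plain wording, the powered contrast is not clearly the one that will be tested.

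Separately, each participant's baseline intake should be known and would be expected to predict later intake. A t test on follow-up values discards that information. With about 30 per arm, what is at stake is precision, and possibly the planned 80% power.

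The same sentence also names a paired test for independent groups. That is a different fault. Here the between-group test is taken to be the ordinary two-sample one, and the point stands after that correction.

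**Working it through.** **Inputs from the Protocol article (Sample size estimation):** differences of 125 g/day (fruit and vegetables) and 15 g/day (protein); 29 and 30 per group; 80% power; two-sided alpha 0.05; 15% loss; 35 per group enrolled.

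**Assumed, because not in the document:** the correlation r between baseline and follow-up intake, taken from 0.3 to 0.8, with equal variance at the two times.

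**Step 1: the plan's own figures.** Without an SD, 29 and 30 cannot be reproduced forwards. Solving σ = δ·√(n/2) / (1.960 + 0.842) backwards:
- Protein: 15 × √15 / 2.802 = 20.7 g/day (20.4 with the noncentral t).
- Fruit and vegetables: 125 × √14.5 / 2.802 = 169.9 g/day (167.0 with the noncentral t).

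The standardised effects (noncentral t) are about 0.74 and 0.75. On loss, 30 × 1.15 = 34.5 gives 35, while 30/0.85 = 35.3 would give 36. With 35 enrolled and 15% lost, 35 × 0.85 = 29.75 per arm remain, so about 30 is a fair working number.

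**Step 2: variances.** With single-visit variance σ²:
- visit-only comparison: σ²
- change score: 2(1 − r)σ²
- ANCOVA on baseline: (1 − r²)σ²

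So ANCOVA has (1 − r²) times the visit-only variance: 0.91, 0.75, 0.51 and 0.36 at r = 0.3, 0.5, 0.7 and 0.8. Relative to change scores the ratio is (1 − r²)/[2(1 − r)] = (1 + r)/2: 0.65, 0.75, 0.85 and 0.90. Visit-only variance exceeds change-score variance when 1 > 2(1 − r), that is, when r > 0.5.

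**Step 3: reading A, the implied SD is that of change** (as Sample size estimation words it). Protein, 30 per group, noncentral t; single-visit SD = 20.4/√(2(1 − r)).

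| r | single-visit SD (g) | visit-only power | change-score power | ANCOVA SD (g) | ANCOVA power |
|---|---|---|---|---|---|
| 0.3 | 17.2 | 91.2% | 80.0% | 16.4 | 93.5% |
| 0.5 | 20.4 | 80.0% | 80.0% | 17.7 | 89.9% |
| 0.7 | 26.3 | 58.3% | 80.0% | 18.8 | 86.0% |
| 0.8 | 32.2 | 42.6% | 80.0% | 19.3 | 84.0% |

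Fruit and vegetables at 29 per group give the same powers to the decimals shown. At 29.75 per arm, protein becomes 91.0/79.7/58.0% (visit-only) and 93.3/89.6/85.7% (ANCOVA) at r = 0.3/0.5/0.7. For 80% power at r = 0.7, the visit-only test needs 50 per group (protein) or 48 (fruit and vegetables); ANCOVA needs 26 or 25.

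**Step 4: reading B, the implied SD is that of a single visit.** Protein, 30 per group.

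| r | visit-only power | change-score power | ANCOVA SD (g) | ANCOVA power |
|---|---|---|---|---|
| 0.3 | 80.0% | 65.8% | 19.5 | 83.6% |
| 0.5 | 80.0% | 80.0% | 17.7 | 89.9% |
| 0.7 | 80.0% | 95.1% | 14.6 | 97.5% |
| 0.8 | 80.0% | 99.3% | 12.2 | 99.7% |

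The ANCOVA powers ignore the one degree of freedom spent on baseline, which is negligible against 58.

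**The case against.** **The mismatch may be only apparent.** The between-group differences at 3 and 6 months could mean differences in change, since the sizing section describes the primary outcomes as changes. If so, the planned and powered quantities agree. The wording allows this but does not say it, so the mismatch is possible rather than proven. The precision argument survives, because ANCOVA also has smaller variance than a change-score comparison over the whole assumed range.

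**An unadjusted comparison is valid, and covariates often wait for the analysis plan.** Its validity under randomization is not disputed; what is lost is efficiency. But the article does not leave the method open: it names the comparison, the visits and a test that takes no covariate.

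**The harm is not consistent.** This stands. Under reading A with r = 0.3, the visit-only test has 91%, above plan and close to ANCOVA. Under reading B it keeps exactly 80%.

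**Stronger readings that the document does not support:**
- A reader might infer that leaving out treating dentist also costs precision. No between-dentist variance is given, randomization to diet group is not described as stratified by dentist, and these dentists give no advice and assess no outcomes. Any gain is unshown.
- A reader might infer that baseline intake is known to vary widely. The Discussion says only that some high-intake participants might enter; it gives no spread.
- A reader might infer that a chance baseline imbalance carries over in full to the follow-up difference. With equal variances the expected carry-over is r times the imbalance: 30% at r = 0.3 and 70% at r = 0.7.

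**Conclusion.** The point holds as a matter of precision and of unclear alignment between sizing and analysis. It is an improvement the sponsor should make, not a correction of an invalid test.

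Baseline adjustment reduces variance relative to the visit-only test by 9%, 25% and 51% at r = 0.3, 0.5 and 0.7, whichever SD the sizing used. The power consequence is conditional: the visit-only test drops below 80% only if the implied SD is that of change and r exceeds 0.5, for example to about 58% at r = 0.7. It would therefore be wrong to conclude that the trial is underpowered as planned. The implied SDs are back-calculated and r is assumed; the document gives neither.

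**What to change.** In Statistical analysis, replace the between-group t test with one prespecified baseline-adjusted model for each primary intake. Either of these would serve:
- ANCOVA of intake at the visit on group, with the same intake at baseline as covariate; or
- a linear mixed model over 3 and 6 months with group, visit, group-by-visit and baseline intake.

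The sponsor should name one of them. Use the same model for secondary outcomes that have a baseline value. Treating dentist may be added, but this is optional.

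In Sample size estimation, say whether the SD behind 29 and 30 per group is for change or for a single visit, give it with the assumed correlation, and state power for the model chosen.

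The cost is a few sentences and one degree of freedom for baseline, with no new data. The article reports that recruitment is under way, so the change should be fixed before group outcomes are compared. It does not settle which of the two visits is primary; that needs its own statement.
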